## Abstract

**Background:**

Despite numerous reports of significant distress and burden for hematopoietic stem cell transplantation (HSCT) patients and caregivers (CGs), HSCT-specific coping interventions remain rare. The few in use lack specificity and are often not easily accessible or cost-effective. Whereas the development of new interventions is resource-intensive, theory-informed adaptation of existing evidence-based interventions is promising. To date, no HSCT-specific intervention has relied on a formal adaptation approach.

**Methods:**

Using the Center for Disease Control and Prevention’s Map of Adaptation, this two-phase qualitative descriptive study seeks to understand the perceptions of HSCT patients, CGs, individually, and in dyads, and clinicians about *Coping Together* (CT) for the preliminary adaptation (Phase 1), and then explores perceptions of the modified intervention in additional mixed sample (Phase 2). Six to ten participants including outpatients, CGs and dyads and five to seven HSCT clinician participants will be recruited for Phase 1. For Phase 2, 14 to 16 participants including outpatients, CGs and dyads will be recruited. Individual and dyadic semi-structured interviews will take place between 100 and 130 days post-HSCT. Verbatim transcripts will be analyzed using content analysis.

**Discussion:**

It is paramount to have HSCT-specific supportive interventions that address patients’ and CGs’ multidimensional and complex needs. The timely involvement of key stakeholders throughout the adaptation process is likely to optimize the relevance and uptake of such tailored intervention.

**Trial registration:**

This study is registered on October 6, 2016 in ClinicalTrials.gov at (identifier number NCT02928185).

## Background

In 2015, nearly 20,000 autologous (self-donor) and allogeneic (related or unrelated donor) hematopoietic stem cell transplantations (HSCTs) were performed in the US with expectations of a continued upward trend [1]. HSCT for hematologic malignancies, such as leukemia, lymphoma, multiple myeloma, myelodysplastic syndrome and aplastic anemia, is a potentially curative procedure, and in cases of refractory or advanced disease, remains the last hope [2]. Traditionally, HSCTs have been inpatient procedures due to intensive treatment regimens and a complex recovery process. However, feasibility, cost containment, and patients’ needs and quality of life issues have mandated a shift to outpatient settings [3–5]. This shift means more intensive involvement of caregivers (CGs).

With an increasing number and complexity of role demands, CGs are challenged to perform their role while balancing other demands with limited preparation and support [6]. CGs, therefore, are prone to illness-related distress, unmet needs and coping difficulties that often exceed that of patients [7–9]. Frequently, the necessity of balancing competing demands leads to levels of distress (anxiety, depression) that are comparable to psychiatric inpatients, thus compromising the caregiving role [10, 11]. In addition, concerns prevail about the perseverance of HSCT CGs to sustain their vital role over a prolonged course and how to support them most effectively.

Acknowledging the shared cancer experience of patients and CGs, clinicians and researchers alike have begun exploring intervention development from a dyadic perspective [12]. Conceptualization of cancer as a disease affecting more than the patient emanates from the notion that “illness is something that happens to the couple and that the focus on patient and partner separately may not be as beneficial from a theoretical and clinical perspective as a focus on the relationship” ([13], p., 2542). Evidence suggests that positive dyadic coping can enhance patients’ and partners’ psychosocial adjustment [14, 15]. Hence, coping strategies adopted by patients facilitate their own well-being as well as their partners’ and vice versa [16, 17].

Thus, couple-based interventions (CBIs) that involve dyads, namely patients and their spouse/partners, are promising in terms of diminishing psychological distress associated with a stressful chronic illness such as cancer [18]. However, CBIs have rarely been integrated into routine care due to several barriers including patients being too busy to participate, limited intervention access, the lack of tailored interventions and costs related to reliance on trained professionals [14, 15, 19].

Moreover, limited intervention access is evident in the HSCT population. In a randomized control trial (RCT) with 148 partners of allogeneic patients, Laudenslager et al., reported positive outcomes with a modified version of a psychosocial intervention on psychological and physiological distress, anxiety and depression during the first 3 months post-HSCT [20]. CGs in the intervention group demonstrated a downward trend in psychological distress, anxiety and depression over 3 months with effect sizes ranging from 0.39 to 0.66 [20]. Despite the favorable impact of the intervention, researchers’ costs ranging from $300 to $350 per participant hindered sustainability. In another HSCT invention study, Bevans et al., demonstrated the feasibility of an individualized problem-solving education intervention during the first 4 weeks after discharge home [21]. However, in addition to excessive researcher costs, they also cited challenges in coordinating schedules between the researcher and the participants, and time constraints of CGs who need to balance multiple roles [21]. Furthermore, none of the cited studies detailed the adaptation process for their respective intervention.

Recently, self-directed (unguided or without a researcher/clinician involved in delivery; also known as self-administered, self-help) interventions have been suggested as a cost-sparing, flexible, accessible and promising delivery modality for cancer dyads [22, 23]. The self-directed delivery modality allows users to self-determine what (content), when (time), where (location) and how (individually or jointly) to use the intervention booklets. Therefore, self-directed delivery formats can provide HSCT patients and CGs the benefits of flexibility in timing and diminish potential information overload [24].

### The *Coping Together* (CT) intervention

CT is an evidence-informed, self-directed individual and dyadic coping skills intervention that has been developed in Australia to enhance adaptive coping strategies for heterogeneous cancer patients and partners confronting physical and psychosocial challenges [25]. Preliminary data from a pilot study demonstrate positive trends for CT patients in decreasing distress (intrusion and avoidance) and appraising cancer as significantly less challenging, whereas, for partners, CT was related to lower caregiver stress, reduced financial strain and improved illness-related appraisal [19]. In an ongoing RCT, the efficacy of CT is examined in prostate, breast, colorectal and early stage melanoma patients and their partners as a multimedia intervention comprises of six booklets, a DVD of key content, a relaxation CD and a website [23]. The series of six CT booklets addresses: (1) symptom and side effect management; (2) developing quality relationships with healthcare providers; (3) soliciting additional support; (4) improving cancer-related communication pathways; (5) contending with emotions and worries; and (6) coping with treatment-related decisions. Each booklet presents cognitive-behavioral therapy-based exercises to facilitate tailored coping strategies, suggestions for contending with potential stress-inducing situations, anecdotal accounts, and suggestions from clinicians [23].

### Adaptation of the *Coping-Together* booklets

Adaptation is the process of modifying an evidence-based intervention to minimize disparities between its characteristics and those of the new target group [26]. Intervention adaptation can be minor (e.g., changing the name) or substantial (e.g., revising its clinical or cultural evidence). The adaptation process of the CT booklets will retain the core components that produce its intended outcomes, such as the enhancement of adaptive coping skills and greater confidence in the use of these skills, individual and dyadic involvement, and adoption of new pragmatic coping strategies [27]. Whereas key characteristics, important attributes of the intervention, will be adapted according to clinical judgment and recommendations of participating HSCT patients, CGs, dyads and clinicians [27]. Key characteristics will include the multimedia format, structure (e.g., length), content (e.g., HSCT-related information, coping skill strategies), information presentation (e.g., font size, text boxes, visuals), cognitive-therapy based exercises, and supportive narratives. The booklet concerning treatment-related decisions will be excluded, as this is irrelevant during the post-HSCT recovery phases.

### CDC’s Map of Adaptation guidelines

The CDC’s Map of Adaptation is a systematic approach that emphasizes implementer and clinician involvement to ensure adaptation and tailoring to the target group [27]. The Map of Adaptation also allows feedback loops to ensure adaptation is tailored to the new target population and flexibility in step sequence (allowance for non-sequential, simultaneous step sequence) [27]. For this study, the first three steps will be completed, which are instrumental for informing the acceptability of the intervention; intervention refinement and laying the foundation for subsequent pilot intervention studies [28–30]. The Steps of the Map of Adaptation guidelines are detailed below.

Step 1 called “*Assess*” involves three parts. Part 1 comprises a literature review of the target population focusing on their needs, socio-demographics and recent trends (treatment-related, health-seeking behaviours), as well as determining the suitability of the intervention for the target population and any barriers potentially limiting access to the intervention. Part 1 can include interviews of key stakeholders. Part 2 entails a literature review of potential interventions that can meet the target population’s needs. In Part 3, the organizational capacity to adapt and implement the intervention is reviewed by considering its philosophy (mission, values), experiences (with the target population, implementing interventions) and resources (staff, supplies, space, funding).

Step 2 called “*Select*” evaluates the recommendations from Step 1, and then finalizes the decision regarding which intervention will be adapted. In most cases, there are discrepancies among the target population, intervention and organization, thereby directing the need for adaptation that can be minor such as the revision of a term used, or substantial such as revising the intervention’s cultural relevance for the new setting.

Step 3 called “*Prepare*” involves three parts. In Part 1, an adapted intervention based on the stakeholders’ recommendations is generated. In Part 2, participants’ experiences with the adapted intervention are pre-tested for further refinement to ensure tailoring and cultural appropriateness of materials. Part 2 focuses on content, language translation, intervention renaming, incorporating local proverbs and anecdotes, as well as identifying potential implementation issues, such as delivery modality, literacy level, layout, and clarity of instructions. In Part 3, the organization is prepared to ensure successful implementation by recruiting and training additional staff, obtaining (different) space, assembling materials, securing more funding, and strengthening partnerships and collaborations.

Step 4 called “*Pilot*” and Step 5 called “*Implement,*” which involve testing and implementing the adapted intervention, respectively, will not be discussed in detail as they are beyond the scope of this study. Furthermore, Phase 1 of this study will include Steps 1, 2 and 3, Part 1 to generate the HSCT-adapted CT intervention (hereafter cited as HSCT CT), and Phase 2 will include Step 3, Parts 2 and 3 to refine the HSCT CT booklets (Fig. 1).

**Fig. 1 Fig1:**
[figure not shown]
Summary of the CDC’s Map of Adaptation Guidelines

### Study aims and research questions

This two-phase descriptive qualitative study will expand the current literature by using the CDC’s Map of Adaptation guidelines to systematically adapt the CT booklets for the HSCT context. Phase 1 will gather the perceptions of participating HSCT patients, CGs, dyads and clinicians about the unmodified CT booklets for preliminary adaptation. Phase 2 will explore the experiences of an additional sample of HSCT patients, CGs and dyads to further refine the HSCT-adapted CT booklets.

Specifically, this study poses three research questions:Guided by the CDC’s Map of Adaptation, what are the perceptions of HSCT patients, CGs, dyads and clinicians about the unmodified CT booklets in the early post-HSCT period?;What needs to be understood about the participants’ perceptions about the unmodified CT booklets?; andWhat are the participants’ perceptions/experiences with the HSCT-adapted CT booklets during the first 100 days post-HSCT?

## Methods/design

### Study design and setting

The study employs a qualitative descriptive design. Participants will include patients in the first 100 days after being treated for an outpatient HSCT at Memorial Sloan-Kettering Cancer Center (MSKCC) in New York City, USA. The study design is illustrated in Fig. 2. For this study, CG will be defined as spouse, partner, family member, friend, colleague, or neighbor who provides uncompensated medical (e.g., aseptic central line care) and custodial (e.g., preparing low microbial diet) care who might, but does not necessarily lives with the patient [31–33]. A dyad will be defined as a combination of a patient and their designated CG. Patients will be included if they are admitted to the Adult Bone Marrow Transplantation (BMT) service for an outpatient HSCT for a hematologic malignancy. Other inclusion criteria for patients and CGs will be age greater than 18 years; ability to read, speak and understand English; and physically and cognitively able to participate in the study. CGs will be excluded if they are unable to fulfill caregiver responsibilities for more than 50% of the time (> 50 days). Dyads will be included if patients and CGs mutually agree to participate in the study.

**Fig. 2 Fig2:**
[figure not shown]
Study Schemas

### Phase 1: Preliminary adaptation of the CT booklets

#### Recruitment of Phase 1 HSCT patients, CGs and dyads

A convenience sample of six to ten patients, CGs and dyads will be recruited. Data saturation will not be attained since the objective is to obtain diverse perspectives of key stakeholders with the unmodified CT booklets for the preliminary adaptation per the CDC’s Map of Adaptation guidelines.

#### Procedures for recruitment of Phase 1 HSCT patients, CGs and dyads

The first author will screen potential participants who are listed on the weekly BMT admission schedule and then, will present the study at an introductory meeting during which questions will be answered. Amenable participants will sign the consent form and complete a socio-demographic questionnaire. Each participant will be provided a copy of the signed consent form.

Within 1 month prior an outpatient HSCT, the first author will deliver an intervention pack containing the following: (a) five unmodified CT booklets (one set for HSCT patients and CGs and two sets for HSCT dyads); (2) instructions on how to use the booklets; (3) instructions to review the content and mark up the copies ad lib with handwritten comments and recommendations; and (4) a reminder to bring the annotated CT booklets to the interview to facilitate the discussion. Between 50 and 75 days post-HSCT, the first author will remind HSCT patients, CGs and dyads to review the CT booklets. This communication will be a prompt only and not for therapeutic counseling. Between 90 to 100 days post-HSCT, the first author will contact participants to arrange individual or dyadic interviews that will take place between 100 and 130 days post-HSCT.

#### Data collection of Phase 1 HSCT patients, CGs and dyads

Qualitative data will be collected from semi-structured interviews, supplemental interview notes, and documents (annotated booklets). All participants will also complete a socio-demographic questionnaire.

Between 100 and 130 days post-HSCT, the first author will conduct semi-structured, face-to-face or telephone, individual and dyadic interviews to describe the participants’ perceptions about the content, structure and process of the unmodified CT booklets and recommendations for the preliminary adaptation. The interview format – face-to-face versus telephone -- will be based on each participants’ convenience to reduce study burden.

Following an interview guide, participants will be queried with open-ended questions designed to address the research focus (Table 1). Questions will be intentionally broad and open-ended to encourage participants to share their own perspectives. Flexibility in the question sequence will be allowed to facilitate conversation flow. Interview techniques will include (1) probes to increase data richness and depth of responses; (2) interpreting questions based on cues from something said, alluded to or to revisit an issue superficially discussed; (3) explicating the implied (repeating what has been said in the form of a question) to facilitate elaboration; and (4) silence to allow for reflection and formulation of responses [34]. Probes will be used to ensure feedback is obtained from each dyadic member. Interviews will be audio-recorded, transcribed verbatim by a professional transcription service and supplemented by interview notes. Estimated duration of interviews will be 60 min. The annotated booklets will be collected and reviewed to corroborate information from the interviews and for data source triangulation.

**Table 1 Tab1:** Summary of Phase 1 Semi-Structured Interview Questions

Participants	Interview Questions
HSCT Patients or CGs	• Could you please tell me what it has been like during the first 100 days after HSCT? • How did you use the booklets during the first 100 days after HSCT? • Approximately how much of each booklet (percent or number of pages) would you estimate that you reviewed? If you didn’t review the booklets, could you please tell me the reason(s)? • What was helpful/least helpful? • How did you find using these booklets on your own? Would it have been better to use them together? • What did you think about the • Layout? • Appearance? • Information? • What would you keep/remove? • What other recommendations would you make?
HSCT Dyads	• Could you please tell me about your experiences as a couple within the first 100 days post-HSCT? • Can you describe how you cope with difficult situations as a couple? • Approximately how much of each booklet (percent or number of pages) would you estimate that you reviewed? If you didn’t review the booklets, could you please tell me the reason(s)? • How much of the time did you use the booklets together? And as individuals? • What content will be helpful to you as a couple? • What content will be least helpful as a couple? • What changes do you recommend?
HSCT Clinicians	• Could you please tell me what you think about the content of the CT booklets for HSCT patients, CGs and dyads? • Could you give me examples of what you think will be helpful/least helpful? Why? • What do you think are the advantages/disadvantages of the self-directed format for HSCT dyads? • What information do you think is missing? • What changes would you recommend?

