#### Data analysis Phase 1 HSCT patients, CGs and dyads

Qualitative data will be analyzed using inductive Qualitative Content Analysis (QCA) and NVivo® (QSR International, Doncaster, Australia) to obtain a comprehensive, descriptive summary of opinions, perceptions and experiences in the words of the participants [35]. QCA will identify themes for recommendations for adapting the CT booklets. Data from the interviews will be analyzed separately, and then compared for discerning differences in the participants’ perceptions as well as areas of consensus on changes to be integrated into the booklets. Intra-dyadic comparisons will be conducted to discern similarities and differences between joint and individual recommendations and perceptions. Dyadic data of each member will also be compared with recommendations from individual HSCT patients and CGs, respectively. Data collection and analysis will be conducted concurrently and sequentially in the following three phases:

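### The Phase 1 dyad questions in Table 1 do not match the protocol's own dyad definition, interview timing and interview scope, which weakens the planned comparison of dyads with individuals

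*Protocol article*

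**What the plan says.** **Who forms a dyad.** Under 'Study design and setting', "CG will be defined as spouse, partner, family member, friend, colleague, or neighbor who provides uncompensated medical" and custodial care. The same section states: "A dyad will be defined as a combination of a patient and their designated CG". A dyad therefore need not be a marital or romantic pair.

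**What Phase 1 dyads are asked.** The dyad row of Table 1 opens with "Could you please tell me about your experiences as a couple within the first 100 days post-HSCT". It later asks "What content will be helpful to you as a couple", followed by the same question about the least helpful content. Its last item is an open question on recommended changes.

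**What Phase 1 individuals are asked.** Patients or caregivers interviewed alone are asked "What was helpful/least helpful" and "What did you think about the • Layout? • Appearance? • Information". They are also asked what they would keep or remove and what else they would recommend.

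**When and why.** Under the Phase 1 recruitment procedures, booklets arrive within one month before transplantation, a reminder follows at days 50 to 75, and interviews take place at days 100 to 130. The data collection section gives individual and dyadic interviews one shared purpose: perceptions of the booklets' content, structure and process, plus recommendations.

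**How the data are used.** Under the Phase 1 data analysis: "Dyadic data of each member will also be compared with recommendations from individual HSCT patients and CGs, respectively". The same section also plans a wider comparison of perceptions across interviews.

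**The concern.** An interview guide is the measuring instrument of a qualitative study. If two groups are to be compared, a difference in themes is interpretable only if both had a similar chance to raise the theme. Here that chance differs in three ways.

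- **Form of address.** A patient whose caregiver is a sibling or neighbor is asked how the two of them cope as a couple. Such a pair must reinterpret the question or may be put off by it.
- **Tense.** Dyads are asked for a forecast where individuals are asked for an experience.
- **Topics.** Individuals are prompted on presentation and on what to keep or remove, and dyads are not. Yet the section on adapting the booklets lists structure and information presentation among the characteristics to be adapted.

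At stake is how to read any dyad-versus-individual difference on these topics, and whether non-partner dyads can answer comfortably. Phase 1 recruits only six to ten patients, caregivers and dyads and does not seek saturation, so a topic that is not raised is unlikely to be recovered by further Phase 1 interviews.

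**Working it through.** The plan gives no figure to reproduce on this point. The check sets the two Phase 1 rows of Table 1 side by side and compares them with the definitions, timing and purpose stated elsewhere in the article.

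| Topic | Individual patient or caregiver (8 items) | Dyad (7 items) |
|---|---|---|
| Experience of first 100 days | Asked, neutral wording | Asked, as a couple |
| Coping with difficult situations | No item | Asked, as a couple |
| Extent of booklet review | Asked | Asked |
| Manner of use, alone or together | Asked (two items), past tense | Asked, past tense |
| Helpful content | Past tense | Future tense, as a couple |
| Least helpful content | Past tense (same item as helpful) | Future tense, as a couple |
| Layout, appearance | Asked | No item |
| Information | Asked | Partly covered by the two content items |
| Keep or remove | Asked | No item |
| Recommended changes | Asked | Asked |

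**Counts in the dyad row.**
- Couple wording: experiences, coping, helpful, least helpful = 4 of 7.
- Future tense: helpful, least helpful = 2 of 7, both also among the four above.
- Items with neither feature: 7 − 4 = 3 (extent of review, manner of use, recommended changes).

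**Time with the booklets before interview.** The shortest possible time is 0 + 100 = 100 days, if the pack arrives on the day of transplantation and the interview is on day 100. The longest is about 30 + 130 = 160 days, taking one month as 30 days. On any schedule the plan allows, the dyad has had the booklets for at least 100 days, so a question about what will be helpful does not fit. The clinician row uses the same future tense, which is natural there because clinicians review the booklets without using them as patients or caregivers.

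**Phase 2 for contrast.** The dyad row of Table 2 does not use couple wording. It asks about use and help *together*, asks in the past tense how the booklets helped, and includes a keep-or-remove item. The form-of-address and tense problems are therefore confined to Phase 1. Neither row of Table 2 has a specific item on layout or clarity of instructions. The article's account of Step 3, Part 2 of the adaptation guideline, which Phase 2 covers, mentions "identifying potential implementation issues, such as delivery modality, literacy level, layout, and clarity of instructions".

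**Effect on the comparison.** The topics common to both Phase 1 rows (extent of review, manner of use, helpful and least helpful content, recommended changes) can still be compared, with a caveat on tense for helpful and least helpful. Layout, appearance and keep-or-remove are prompted on one side only.

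**The case against.** The strongest reply has four parts.

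1. **Tables 1 and 2 are titled summaries of semi-structured guides.** The full guides and their probes are not shown, so it cannot be said that dyads are never asked about layout. This stands, and the omission can be claimed only for the guides as summarised. It does not help with the couple wording or the tense, which are printed in the summary itself.

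2. **The interviews are flexible.** Questions are broad, probes and cue-based follow-up are planned, the dyad row ends with an open question on changes, and dyads receive two sets of booklets to annotate. This mitigates in part. The flexibility expressly stated concerns the order of questions, and the dyad-specific probe ensures that each member is heard, not that each topic is covered. Annotation is at the participant's discretion. The annotated booklets serve to corroborate the interviews, while the stated unit of analysis is the transcripts and supplemental notes.

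3. **Dyadic and individual interviews may reasonably have different foci, and the tense is a small matter.** The dyad item just before the two forward-looking ones asks about past use, so the context is set. This is fair, and it keeps the tense point small. It does not explain why prompts on structure should differ when the two interview types share a stated purpose.

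4. **The guideline text does not require a layout question.** This stands. The article offers layout and clarity of instructions as examples, and Phase 2 asks everyone what needs changing and what to keep or remove, so such comments can surface there.

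A reader might also infer that fit for non-spousal caregivers is the main adaptation gap, since the intervention was developed for patients and partners. The article does not rank the characteristics to be adapted and does not list caregiver relationship among them, so that inference is unsupported.

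**Conclusion.** The point holds as a mismatch between the Phase 1 dyad questions and the protocol's own definitions and schedule. Four of seven questions presume a couple where the definition does not; two of those four ask for a forecast about booklets held for at least 100 days; and layout, appearance and keep-or-remove are prompted for individuals only.

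The consequence is a weakened comparison. A reader might infer that the planned comparison fails altogether, but the documents do not support that: both rows elicit recommendations, extent of review, and helpful and least helpful content, and recommendations are what the quoted comparison names. The weakness is limited to topics prompted on one side and, to a lesser degree, to the two items that differ in tense. On these, a difference between dyads and individuals could reflect the question set rather than perceptions.

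The counts are certain because they come from the printed tables. The statement on missing prompts assumes that the summarised rows reflect the working guides. How often the couple wording would misfit depends on how many enrolled dyads are not partners, which the article does not estimate.

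**What to change.** In the Phase 1 dyad guide:

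- Replace the couple wording in the four affected questions with neutral wording such as 'together', as the Phase 2 dyad guide already does.
- Put the helpful and least helpful questions in the past tense, matching the individual guide.
- Add the layout, appearance and keep-or-remove prompts used for individuals. Dyad-specific questions can stay alongside them.

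Optionally, add one prompt on layout and clarity of instructions to both rows of Table 2, in line with the article's description of Step 3, Part 2. If the working guides already contain these prompts, a sentence saying so would settle that part.

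A planned comparison of spousal with non-spousal caregivers is not recommended. With six to ten patients, caregivers and dyads in Phase 1, the groups would be too small to be informative.

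The cost is a minor amendment to the interview guide and a few more minutes in an interview estimated at 60 minutes. If some Phase 1 dyads have already been interviewed, the report should say which version of the guide each received.
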